### **Health economics in case–control study**

The study provides a unique opportunity to examine the health care costs longitudinally of this group of patients compared to a normal distribution of patients. The health and resource patterns for regular attenders have not been compared to the resource cost for a normal population before. This work will give a real opportunity to establish the true cost to society of a regularly attending group of patients. Whilst health economics does not generally consider burden of illness studies, unless the true resource costs of this group of patients are known, we cannot establish the likely willingness to pay for an intervention that may reduce the costs incurred by these regularly attending patients. Logically any intervention that costs less than the current annual treatment cost for regular attenders will at least probabilistically be potentially cost effective.

We will examine health and social care costs over the preceding 10 years from primary care records in both the regular attenders and normal attenders who have consented to the study. For each preceding year over the last 10 years, information will be collected on the number of contacts and missed appointments with the GP (at surgery, home or telephone contacts), practice nurse, community nurses, counsellors, physiotherapists, occupational therapists, social workers, community workers, NHS Direct, drop-in centres and home help, prescriptions, investigations, secondary care in-patient and out-patient care, and emergency care. Practice based primary care information is likely to be more accurately recorded than contacts that happened outside the practice. However we intend to trawl for the GP referral letters to obtain estimates of secondary care usage and we will also collect contact information for each participant from all local hospitals. Full and complete anonymised data sets of ten year medical records will be processed using a replicable method of electronic data collection that has been developed specifically to answer a number of health and economic and clinically important questions. In addition this data will provide us with a detailed insight into patients resource use in primary as well as secondary care. We will be able to check the data retrieved electronically with the data collected from the modified Client Services Receipt Inventory (CSRI) [55] and therefore check the degree to which care outside the practice may be underestimated. Similarly the analysis of reporting of contacts with primary care at interview compared to the primary care record will explore whether or not regular attenders are underreporting health contacts compared to normal attenders as reported previously [21,51]. To examine agreement in some key information of service use between patient recalls and primary care records, we shall use non parametric correlation analysis which includes Spearman’s rank correlation coefficient, Kendall tau, and Kappa coefficient for different outcome measures where it is appreciated. We will explore the effect any under-reporting by regular attenders may have had on health and social care costs.

We will ascertain health, social and personal costs using the modified CSRI [53] and also quality of life and cost utility on the EQ5D [54] over the three months preceding baseline interview in both the regular attender and normal attender control groups. Services measured will include secondary care mental and physical care, primary care, accident and emergency and other out of hours or direct access services such as NHS Direct, NHS walk-in centres, services provided by councils, other social care agencies, voluntary agencies and complementary therapy. In addition, inputs provided from family members as a result of the patient’s health problems will be recorded and the amount of time off work by the patient and any carer due to ill health will be recorded and costs attached. Other costs include out-of-pocket expenses (such as travel to seek health care), expenditure on 'over-the-counter' medicines, the extent of informal care (for children or the house) and any other costs (such as informal care, heating from being at home when off work and costs to carers). Data on social security payments will also be collected. Prescribing data will be obtained from primary care patient records and patient interview. Nationally applicable unit costs [57] will then be combined with the service use data to generate service costs for primary care. Medication costs will be obtained from the British National Formulary, and hospital based costs will be obtained from NHS reference costs/PBR (payment by results). Costs of time off work will be calculated from the patient’s own account of their salary and normal expectations of overtime and informal care to the patient will be calculated using the carer’s wage rate where possible or alternatively at the commercial rate that a carer would have normally expected to be earning at that time. Cost data will be combined with utility weighted health-related quality of life data as recorded by the EQ5D [54].

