### **Case control study of regular attenders and normal attenders**

#### **Inclusion criteria**

1. Regular attenders

· 30 or more face to face contacts with GP within the last 2 years established from the practice electronic record.

· Aged 18 years old and over.

· Consents to take part in the study

2. Normal attenders

· Between six and 22 face to face contacts with GPs over two years, established from the practice electronic record. A previous study of 828 consecutive attenders from eight Nottinghamshire practices revealed a median attendance of eight face to face consultations with GPs with approximately two thirds of the sample consulting between three and eleven consultations. Therefore we selected a normal consulting control group from patients who attended face to face appointments with the GP between six and 22 occasions.

· Aged over 18 years or older

· Consents to take part in the study

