### **Statistical analysis in case control study**

Burton et al. [56] showed that 93 (48%) of patients with MUS diagnosed by secondary care physicians on two or more occasions and referred at least three times in the last five years had depressive and anxiety disorder compared to 38 (25%) patients only referred once to secondary care in the previous five years (odds ratio 2.6 (95% confidence intervals 1.6, 4.1). If these groups are assumed to be similar to the regular attenders and normal attenders in the current study, a sample size of 100 regular attenders and 100 normal attenders will have 90% power to show a difference at the 5 per cent level of significance on two tailed testing.

The regular attender and normal attender groups will be compared on the proportion with mental disorder (depressive disorder, anxiety disorder, somatoform disorder, overall prevalence of mental disorder), mean number of active physical health problems, distribution of severity of health anxiety, proportion of obesity on BMI, mean scores on smoking, alcohol consumption and exercise, and utility related quality of life on the EQ5D. Univariate analysis to test differences between the two groups will be performed using *t*-test for group means or geometric means if logarithm transformation is required for variables with skewed distribution. Chi-squared test will be used for group differences in categorical variables. The accuracy of recall by patients over the previous three months will be compared to health care contacts recorded in the primary care record. There is some evidence that regular attenders may not accurately recall health care contacts and do not realise how frequently they are attending compared to practice records [21,51].

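### The coefficients named for recall-record agreement (Spearman, Kendall tau, Kappa) cannot show whether, or by how much, regular attenders under-report contacts

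*Protocol article*

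**What the plan says.** In the protocol article, the section Health economics in case–control study makes three statements close together.

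- **Question.** Comparing contacts reported at interview with the primary care record "will explore whether or not regular attenders are underreporting health contacts compared to normal attenders as reported previously".
- **Method.** "To examine agreement in some key information of service use between patient recalls and primary care records, we shall use non parametric correlation analysis". The sentence goes on to list Spearman's "rank correlation coefficient, Kendall tau, and Kappa coefficient for different outcome measures where it is appreciated".
- **Use.** "We will explore the effect any under-reporting by regular attenders may have had on health and social care costs".

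The section Statistical analysis in case control study returns to the topic: "The accuracy of recall by patients over the previous three months will be compared to health care contacts recorded in the primary care record". It names no method for this. It does give the expected direction of error, citing evidence that regular attenders "do not realise how frequently they are attending compared to practice records".

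The groups are selected on different ranges. Regular attenders need "30 or more face to face contacts with GP within the last 2 years established from the practice electronic record"; normal attenders need between six and 22 over two years.

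**The concern.** The question and the use both need a signed quantity: how many contacts patients leave out, and whether that differs between groups. Spearman and Kendall measure whether patients are ranked in the same order by recall and by record. Patients who all omit the same share, or the same number, of contacts keep their order. The coefficients also depend on how widely the counts are spread, and the spread differs between the groups by design, so a difference in rho is not a difference in accuracy. Kappa is an agreement index and does react to bias, but it gives neither direction nor size.

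At stake are the answer to the under-reporting question and the reading of the three-month costs, which rest on the patient-reported Client Services Receipt Inventory (CSRI). Some of those items, such as out-of-pocket expenses and informal care, are of a kind that a practice record would not normally verify. The practice-contact comparison is therefore the natural place to measure recall bias.

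**Working it through.** The article gives no figure for the recall analysis, so there is none to reproduce. The checks test the method.

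**Inputs from the article.** The recall window is three months, one eighth of two years. Regular attenders therefore average at least 30/8 = 3.75 GP contacts per window, and normal attenders between 6/8 = 0.75 and 22/8 = 2.75.

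**Assumptions.** Means of 4.5 (regular) and 1.6 (normal) contacts per window, gamma-Poisson counts, and the error patterns given below. None of these is in the article.

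**1. Invariance (no distribution assumed).** Spearman is the Pearson correlation of the ranks. Kendall tau is (concordant - discordant pairs) / all pairs, adjusted for ties. A strictly increasing change to recall alters neither. With records 2, 3, ..., 11 (mean 6.5):

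| Recall | Spearman | Kendall | Mean recall - record | Ratio of means |
|---|---|---|---|---|
| identical | 1.00 | 1.00 | 0 | 1.00 |
| halved | 1.00 | 1.00 | 3.25 - 6.5 = -3.25 | 0.50 |
| two fewer | 1.00 | 1.00 | -2.00 | 4.5/6.5 = 0.69 |
| doubled | 1.00 | 1.00 | +6.50 | 2.00 |

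**2. With noise.** 100 patients, 400 replicates, records gamma-Poisson (shape 8, mean 4.5). Recall = fraction × record × log-normal noise (SD 0.2), rounded. Kappa is for four or more contacts versus fewer.

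| Fraction recalled | Spearman | Kendall | Kappa | Mean difference | Ratio of means |
|---|---|---|---|---|---|
| 1.0 | 0.94 | 0.86 | 0.83 | +0.09 | 1.02 |
| 0.8 | 0.94 | 0.86 | 0.70 | -0.81 | 0.82 |
| 0.7 | 0.93 | 0.85 | 0.56 | -1.28 | 0.72 |
| 0.5 | 0.92 | 0.84 | 0.26 | -2.21 | 0.51 |

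The rank coefficients barely move. The signed difference and the ratio recover the bias.

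**3. Kappa and direction.** Kappa = (po - pe)/(1 - pe). Take 100 patients: 40 yes on both sources, 40 no on both, and 20 yes on the record but no on recall.

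- Under-reporting: po = 0.80, pe = 0.6×0.4 + 0.4×0.6 = 0.48, kappa = 0.32/0.52 = 0.615.
- Over-reporting (the 20 reversed): the same margins swapped, kappa = 0.615.
- Symmetric error (10 each way): po = 0.80, pe = 0.50, kappa = 0.30/0.50 = 0.60.

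The three situations are practically indistinguishable.

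**4. Dependence on spread.** Give both groups the same error: -1, 0 or +1 with equal probability, cut off at zero. With gamma shape from 2 to 20, Spearman is 0.81–0.84 at mean 1.6 and 0.94–0.96 at mean 4.5. A separate run with another nearly unbiased ±1 error gave 0.87 and 0.97. Recall error is the same in both groups, yet the coefficients differ.

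**5. Zero records.** The share of normal attenders with no recorded contact in the window at mean 1.6 is exp(-1.6) = 0.20 for Poisson counts, 1.2^-8 = 0.23 for gamma shape 8 and 1.8^-2 = 0.31 for shape 2. A per-patient ratio, or a log(recorded) offset, is undefined for these patients.

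**The case against.** The strongest reply is that the coefficients are tied only to examining agreement in some key information. The under-reporting question and the cost exploration are separate sentences with no method attached, and this is an article whose analysis plan is not shown. The recall sentence in the statistical section also shares a paragraph with t-tests and chi-squared tests. That reading is possible. It does not rescue the text, because the variables listed for those tests do not include recall error, and the only methods named for comparing recall with records are the three coefficients. The point rests on a named method that does not fit the stated question, not on missing detail.

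Several parts of the reply do stand, and they limit what may be inferred.

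- A reader might infer that the plan would report excellent agreement while half the contacts are missing. That holds for rank coefficients when omission is regular. If each contact is forgotten at random with probability 0.5, Spearman is 0.72–0.85, against 0.95–0.98 at 10% forgotten. Kappa, if applied to contact counts, would also drop. The article does not say which coefficient goes with which measure.
- A reader might infer that normal attenders would look less accurate than under-reporting regular attenders. With equal noise in both groups, halved recall in regular attenders gave Spearman 0.78–0.86 against 0.81–0.84 in unbiased normal attenders. No consistent reversal appears; the coefficients simply fail to separate the groups.
- A reader might infer that the ten-year cost comparison is compromised. It is not: those costs come from primary care records, referral letters, local hospitals and Hospital Episode Statistics. Nor does the article describe a numerical correction for under-reporting; it promises only to explore the effect.
- Recall accuracy is not among the four hypotheses or the seven secondary objectives.

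**Conclusion.** The point holds, at moderate severity. The named coefficients cannot answer whether regular attenders under-report relative to normal attenders, and cannot supply the amount needed to explore the effect on costs. For Spearman and Kendall this follows from their definition and needs no assumption. The lack of direction in Kappa is shown by the 2×2 example. The simulated sizes, such as Spearman moving from 0.94 to 0.92 while the mean error moves to -2.21 contacts, depend on the assumed mean, noise and pattern of forgetting, and serve only as illustration. The exposure is confined to the recall comparison and the three-month CSRI-based costs.

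**What to change.** Reword the recall analysis in the health economics section, and refer to it from the statistical section:

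1. **Main analysis.** Calculate recall minus record for each patient over the three months; report the mean difference with limits of agreement, by group.
2. **Between groups.** Estimate the difference in mean recall error, regular minus normal attenders, with a 95% CI.
3. **Relative size.** Report total recalled divided by total recorded contacts for each group. This is needed beside the difference because equal proportional omission gives unequal absolute errors: at 20% omission, 0.2×4.5 = 0.90 contacts against 0.2×1.6 = 0.32 under the assumed means. Use the group-level ratio, not a per-patient ratio or log(recorded) offset, which fail at zero recorded contacts.
4. **Costs.** Use these estimates when exploring the effect of under-reporting on the three-month costs.
5. **Supplementary.** Keep Spearman, Kendall and Kappa, and say which measure each is for.

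The cost is a change of wording and a few extra lines of analysis. No new data, patients or visits are needed.

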### Qualitative study of patients’ reasons for persistent regular attendance

A central hypothesis of the study is that most regular attendance is initiated by the patient in response to a perceived health problem and that health care seeking is a motivated behaviour that serves a function of high psychological importance to that individual and is also shaped by the experience of health care seeking. Our pilot study CBT case series of eight regular attenders confirms that uncertain and unclear communication by health professionals, and consultations with health professionals that do not address the regular attender’s main health concerns, are likely to increase health anxiety and result in further health care seeking. However, the representativeness of the participants who took part in the CBT case series suggests the need for a specific qualitative study involving maximum variance sampling of patient characteristics.

#### **Recruitment**

A sample of approximately 12 to 15 regular attending patients will be selected for individual qualitative interviews based on age, gender, ethnicity, practice, employment status, marital status, consultations mainly in primary care, emergency care and secondary care, high and low health anxiety, presence and absence of somatoform disorder, presence or absence of depressive disorder, presence or absence of panic disorder, presence or absence of more than one active physical health problem. Sampling will allow participants to meet more than one of these selection criteria. The exact number of participants will depend on the representation in this sampling frame and saturation of themes as they emerge. This purposive sample will be selected from the 100 regularly attending patients that have originally completed a consent to contact form and been recruited to the study. Selected participants will be invited to take part in the qualitative interview by the study researcher who will send them an invitation letter, information sheet and reply slip, along with a stamped addresses envelope. Upon receipt of the reply slip, the researcher will contact the participant, answer any questions they may have, and if verbal consent is given, a time and place for the interview to take place will be arranged. This might be at the participant’s home or at their general practice. Separate written consent for this part of the study will be sought.

### **Procedure and analysis**

The interviews will be carried out by an experienced qualitative interviewer in a private and quiet venue such as the patient’s home or GP surgery. The interviews will be semi-structured according to a topic guide, audio recorded, transcribed and analysed thematically using constant comparison. Catalytic validity will be achieved by using a reference group of researchers from a range of different backgrounds (academic GP, sociology, business school, psychiatry) so that the emerging data can be critically examined and the topic guide is refined according to the emerging thematic analysis. Recruitment of participants to interview will halt when saturation of themes has been achieved.

An individual’s behaviour can be interpreted in terms of its social function for that individual [26,48,50,58].Thus health care seeking can be seen as a motivated behaviour that serves a function of high psychological importance to that individual and is shaped also by the experience of health care seeking. Therefore there is value in understanding temporally the process of the evolution of the symptoms that led to a consultation and what processes are involved in the decision to seek a consultation. The following questions will be explored: How do these differ when a person seeks a consultation to when they do not seek a consultation for a particular set of symptoms? If they did seek a consultation, what were they seeking from the consultation and were those wishes met? How do consultations that meet their needs differ from those that do not? How does the decision to consult primary care and responses from primary care differ if it at all from the decision to consult secondary care or alternative providers?

### **Qualitative study to explore the organisation of care**

The qualitative study of primary care staff will explore how care is currently organised for regular attenders within primary care practices in contrast to other groups of patients such as those with chronic physical health problems or chronic mental disorders. It will explore barriers and drivers to the organisation of care across the practice as outlined in the stepped care interventions that have shown some evidence of effectiveness in randomised controlled trials. Such barriers might be at practitioner level (e.g. attitudes, skills, knowledge, incentives), practice level or policy level.

### **Procedure and analysis**

Two forms of data will be collected. In-depth interviews with purposively sampled participants including GPs, reception staff, practice nurses, practice managers and other primary care professionals will be audiotaped and transcribed. All practices will be sampled so inter-site comparisons can be made. A second body of data will be formed from practice policies, clinical guidelines, memos and any other documents relevant to this clinical group at a national, local or practice level.

Interview data will be analysed through a constant comparison approach. Following first level coding, newly obtained and previously obtained data will be constantly compared back and forth to form categories that will eventually form a narrative concerning the organisation of care of these patients. The information obtained from staff will be contrasted with accounts from patients of seeking help so that areas of agreement and disagreement between patients and different staff members can be explored as they arise in the analysis. Recruitment and analysis will continue until there is a saturation of themes. Data from organisational documents will be subject to content analysis and will be used to illuminate and contextualise the interview data.

### **Pilot intervention study**

The aims of the pilot intervention in the five practices are three fold to:

1. gain a better understanding of the development of regular attendance using CBT formulation (secondary objective 1);

2. develop a descriptive typology of the reasons for regular attendance and the opportunities for therapeutic intervention based on CBT formulation (secondary objective 2);

3. determine the acceptability, feasibility and clinical utility of joint care between the cognitive behaviour therapist and GP based on both the CBT formulation and treatment and a collaboratively agreed treatment plan (GP, cognitive behaviour therapist and patient) (secondary objective 3).

### **Intervention**

The intervention will be offered at one of two levels to all regular attender patients who complete the baseline assessment and case record examination outlined in case study one (Figure 1). It will not be offered to normal attenders. Level 1 intervention will be offered to all regular attenders provided they consent to further assessment and therapeutic intervention by one of three cognitive behaviour therapists, currently have functional somatic symptoms, depressive or anxiety disorders, do not have an urgent need for other health care and are not already receiving mental health care as shown in Figure 1.

In level 1 interventions the cognitive behaviour therapist will formulate the reasons for regular attendance in both primary care and secondary care settings in consultation with the GP who usually sees the patient (Figure 2). In keeping with recent developments in CBT formulation, the latest problem-specific models will be used to formulate or a generic model applied for cross-diagnostic issues [59]. Whichever CBT model is used emergent formulations and intervention plans will focus on addressing three areas: 1. The primary focus of the formulation is on the pattern of regular consultation behaviour of the patient with health services rather than somatic distress or health anxiety; 2. The formulation takes a developmental perspective seeking to understand how the regular consultation behaviour arose and is maintained [60]; 3. Consulting behaviour of the patient is understood primarily in terms of its social function from the patient’s perspective the responses of primary care, secondary care and social environment to the consulting behaviour.

